## Objectives {7}

The multicenter randomized controlled study aims to investigate the effectiveness of the NeuroNation MED training app on the cognitive abilities of patients with MCI. The intervention group (IG) will utilize the app for a duration of 12 weeks, with a recommended training intensity of three sessions per week, each lasting approximately 25 to 40 min. The wait list control group (CG) can receive their regular conventional medical care prescribed by a physician or no medical care at all, but will not have access to the training app or use any other cCT during the study period.

The primary objective of this study is to determine the effectiveness of the training program in improving the cognitive abilities of individuals with MCI. Additionally, the study aims to investigate the influence of the training program on subjective cognitive functioning, health competence, depressive and anxious symptoms, and psychological well-being. Also, the usability of the provided training program will be evaluated. Furthermore, patient diaries will be utilized to gather comprehensive information regarding additional cognition-oriented lifestyle activities and therapies that are not part of the intervention.

Primary research question:Does a 12-week mobile self-administered cCT program improve cognitive abilities of patients with MCI?H0: There is no significant difference in the index score of the screening module of the Neuropsychological Assessment Battery (S-NAB) between IG and CG.H1: There is a significant difference in the index score of the S-NAB between the IG and CG, favoring the IG.

Secondary research questions:Does the use of the mobile cCT program lead to an improvement in depressive and anxious symptoms, subjective cognitive functioning, psychological well-being, and health-related competence in patients with MCI?Are there associations between the usage of the NeuroNation MED app, sociodemographic data, and changes in cognitive and psychosocial outcomes within the intervention group?How do participants within the IG perceive and evaluate the usability of the NeuroNation MED app?

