### Intervention description {11a}

The intervention includes 12 weeks of mobile adaptive and personalized cCT with NeuroNation MED. The individual exercises are performed within the NeuroNation MED app and are developed based on scientific training concepts to address the relevant cognitive domains. This entails defining the training program based on each participant’s cognitive profile and continuously adapting it according to their individual performance within the exercises. In the context of the app, the term “cognitive profile” does not refer to linking data to clinical assessments within the study, but rather to the use of in-app modules that aim to adjust the training plan and show the progress in the categories of the app. A cognitive profile is derived from relative strengths and weaknesses in the four cognitive domains defined by the NeuroNation MED app (i.e., psycho-motor speed, reasoning, attention, memory). Therefore, these in-app modules are aligned with the exercise design of the app. For the various performance assessments in the app, which form the basis of the personalization algorithm, reference values from the NeuroNation App database, which are available aggregated per age group/exercise within the app/in-app modules adjusting the training plan, are used. Furthermore, the NeuroNation MED app offers supplementary content (“NeuroBooster”) providing participants with the option to access 19 different resources on health literacy, performance enhancement, well-being, and relaxation. These resources feature graphical instructions with short animations to demonstrate the correct execution of the exercises.

Participants within the IG can choose from four intensity levels ranging from 25 to 40 min. Trial participants are recommended to undergo a 12-week training program, consisting of three training sessions per week. Each exercise has a net time of 90 s with the net time being the duration the exercise timer is active. However, training sessions can exceed 40 min due to the need for extra time required to work through explanatory texts, educational content, and user guidance.

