### Criteria for discontinuing or modifying allocated interventions {11b}

Each participant of the study will be informed that participation is voluntary and that withdrawal from the study is possible at any time. It will be communicated that withdrawal will have no effect on possible further treatment at any participating institution. The study may be terminated before its intended completion if ethical concerns arise, if there is insufficient recruitment of participants, or if the safety of the participants is compromised or uncertain. Furthermore, termination may occur if changes in accepted clinical practices render it unwise to continue the clinical trial, or if early indications of harm from the intervention are observed.

Since the study follows an intention-to-treat approach, participants in the IG will not be prescribed a fixed amount of training time or session count for using the NeuroNation MED app. At the first appointment, the IG is instructed to adhere to a certain weekly usage duration and frequency of use, but this is not mandatory for study participation and may vary among participants during the intervention period.

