To achieve comparability between the experimental groups at baseline, the IG and CG will be compared in terms of sociodemographic characteristics. The independent samples Welch’s *t*-test will be used for normally distributed metric variables, while the chi-square test will be employed for categorical variables. If a normal distribution is not found in the data collected, the Wilcoxon signed-rank test or Mann–Whitney *U* test will be applied. ANCOVA will be conducted to evaluate the training effects between the IG and CG, using the baseline values as a covariate and incorporating gender, experimental group (IG and CG) as independent variables, and the post-assessment score as dependent variable. Additionally, age and study center will also be examined as covariates. If the data fail to meet the assumptions for performing parametric ANCOVA, non-parametric tests such as the Wilcoxon test or Mann–Whitney *U* test will be applied instead. Effect sizes and confidence intervals will be calculated for the respective statistical tests to enhance result interpretability.

Using the logging data from the NeuroNation MED app, Pearson correlations will be used to examine the relationships between the number of training days, completed training units, and changes in assessments within the IG. Furthermore, one-way ANOVA will be employed to investigate potential associations between usage frequencies and sociodemographic data.

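### The usage-outcome question is answered only by unadjusted Pearson correlations of self-chosen usage with change, which are open to confounding by age, sex and centre and, under some conditions, to regression to the mean

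*Protocol article*

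**What the plan says.** Objectives {7} lists as a secondary research question: "Are there associations between the usage of the NeuroNation MED app, sociodemographic data, and changes in cognitive and psychosocial outcomes within the intervention group". Statistical methods {20a} answers the part on usage and change as follows: "Pearson correlations will be used to examine the relationships between the number of training days, completed training units, and changes in assessments within the IG". It names no covariate for this analysis.

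Sociodemographic data enter separately: "one-way ANOVA will be employed to investigate potential associations between usage frequencies and sociodemographic data".

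For the randomised comparison the same section is more careful: "ANCOVA will be conducted to evaluate the training effects between the IG and CG, using the baseline values as a covariate", with gender in the model and age and study center examined as covariates.

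Usage is left to the participant. Section {11b} states that "participants in the IG will not be prescribed a fixed amount of training time or session count for using the NeuroNation MED app", and section {11a} that "Participants within the IG can choose from four intensity levels ranging from 25 to 40 min".

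**The concern.** Randomisation protects the comparison between arms. It does not protect a comparison of heavy and light users within one arm, and two separate problems follow.

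**Confounding.** Study setting {9} and Recruitment {15} bring together a geriatrics volunteer database, neurology departments, a neuropsychological outpatient clinic, a post-COVID centre and a long-COVID consultation. These groups can differ in age, in how much they train and in how they change over 12 weeks. A pooled correlation may then reflect differences between centres or age groups. The plan allows that usage may vary with sociodemographic data, since it tests for this by ANOVA, but it does not carry those variables into the usage-change analysis.

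**Regression to the mean.** Change contains the baseline score with a negative sign. If usage is related to the observed baseline score, including its transient part, usage and change will correlate even when training has no effect.

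At stake is the answer to a stated secondary question. An association could be reported that does not come from training, or a real one could be masked.

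**Working it through.** **The plan's own figure.** The protocol gives no figure for the usage correlations, so only the IG size is taken from it. Sample size {14} gives 164 + 82 = 246 for an effect size of 0.39, Wilcoxon-Mann-Whitney test, 80% power, two-sided 0.05. With relative efficiency 3/π and a noncentral t, 164 and 82 give 80.1% power and 246 is the smallest such total, so the figure reproduces. n = 164 is used below.

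**Assumptions (not in the documents).** Write ρ for the baseline-follow-up correlation and r for the usage-baseline correlation. The documents give neither. The range used is ρ = 0.6 to 0.8 and |r| = 0.1 to 0.3. Baseline and follow-up variances are equal, and there is no true usage effect.

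**Case A: usage follows the observed baseline score.**
- Correlation of usage with change = −r × √((1 − ρ)/2).
- Example, ρ = 0.7 and r = 0.2: −0.2 × √0.15 = −0.077.
- Rejection rate by Fisher z, standard error 1/√(164 − 3).
- Adjusting for baseline brings the mean partial correlation back to about 0 and rejection to about 5% (simulation, 5,000 runs per setting).

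**Case B: usage follows only the stable true score.**
- Correlation of usage with change is 0, and rejection stays near 5%.
- Partial correlation with the t1 score given baseline = r × √((1 − ρ)/(1 + ρ)) / √(1 − r²).
- Example, ρ = 0.7 and r = 0.2: 0.2 × 0.420 / 0.980 = 0.086.
- Rejection rate by Fisher z, standard error 1/√(164 − 4).

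| ρ | \|r\| | Case A: size of spurious r with change | rejects | Case B: size of spurious partial r | rejects |
|---|---|---|---|---|---|
| 0.6 | 0.1 | 0.045 | 9% | 0.050 | 10% |
| 0.6 | 0.2 | 0.089 | 21% | 0.102 | 25% |
| 0.6 | 0.3 | 0.134 | 40% | 0.157 | 52% |
| 0.7 | 0.1 | 0.039 | 8% | 0.042 | 8% |
| 0.7 | 0.2 | 0.077 | 17% | 0.086 | 19% |
| 0.7 | 0.3 | 0.116 | 32% | 0.132 | 39% |
| 0.8 | 0.1 | 0.032 | 7% | 0.034 | 7% |
| 0.8 | 0.2 | 0.063 | 13% | 0.068 | 14% |
| 0.8 | 0.3 | 0.095 | 23% | 0.105 | 27% |

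In Case A the spurious correlation has the opposite sign to r; in Case B the partial correlation has the same sign as r. Where one analysis is biased the other is not, so agreement between them is informative.

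**Threshold.** Section {21b} sets 0.00783 for secondary outcomes without saying whether it covers these correlations. If it does, the Case A rates at ρ = 0.7 fall from 17% to about 5% (|r| = 0.2) and from 32% to about 12% (|r| = 0.3).

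The confounding by age, sex and centre cannot be sized from the documents.

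**The case against.** The strongest case for the plan has four parts.

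1. **The question is about association.** A Pearson correlation answers that, and the protocol makes no causal or dose-response claim from it. This stands. A reader might infer that the plan intends dose-response evidence, but the documents do not say so.
2. **The regression-to-the-mean mechanism is not shown to operate.** It needs usage to follow the noisy baseline score. The documents give no usage-baseline correlation, and section {11a} says of the in-app profile that "the term “cognitive profile” does not refer to linking data to clinical assessments within the study". This also stands. A reader might infer that the correlations will be spurious because change is always tied to baseline. That does not follow: in Case B the change correlation is unbiased.
3. **Replacing the correlations by a baseline-adjusted regression could be worse.** This stands too. A reader might argue from the phrase "using the baseline values as a covariate" that what is done between arms should be done here. Between randomised arms, baseline adjustment is safe. Usage is not randomised, and adjusting for an error-prone baseline leaves residual confounding (Case B). This is Lord's paradox, and neither choice is right in general.
4. **An article may leave adjusted supplements to a fuller plan.** This carries less weight, because the article does state the method for this question and states it without covariates.

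None of the four answers the confounding by age, sex and centre. It does not depend on the regression-to-the-mean mechanism.

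**Conclusion.** The point holds as a cheap improvement to a secondary analysis within the IG. Unadjusted correlations of self-chosen usage with change, pooled over centres with different populations, are open to confounding by variables that the plan already uses elsewhere.

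Regression to the mean is a conditional addition. With no true usage effect, a nominal 5% test rejects in about 7% to 40% of cases if usage follows the observed baseline score, and in about 5% if it follows only the true score. In the latter case baseline adjustment rejects in about 7% to 52%. All these rates rest on the assumed ρ and |r|, equal variances and n = 164. The documents do not support a claim that the planned correlations are biased by construction, or that baseline adjustment should take their place. The primary comparison is not touched.

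**What to change.** Keep the Pearson correlations. Beside them, within the IG, report a linear regression on usage with age, sex and centre as covariates in two forms:

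- change as the outcome;
- the t1 score as the outcome, with the baseline score as an added covariate.

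Give the usage slope and its confidence interval for each. Label the analysis exploratory and observational, and state in advance that a usage-outcome conclusion will be drawn only where the two models agree.

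The cost is a change of wording, a little more analysis and a less simple result. No new data are needed, since {20a} already uses these covariates for the arm comparison. Confounders outside the model, such as motivation, remain, which is why the observational label is needed.

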### Interim analyses {21b}

An interim analysis will be conducted when the sample size reaches 50 participants. Employing the alpha-spending function, which is a commonly used method for interim analysis in clinical trials, the alpha level was determined to be 0.00305 for the interim analysis and 0.04695 for the final analysis of the primary outcome. The alpha level for the secondary outcomes in the final analysis will be adjusted to 0.00783 using the Bonferroni correction. Also, the sociodemographic data of the participants that were included in the interim analysis will be compared with the total sample using a multivariate ANOVA with the factor participant group (interim analysis vs. remaining participants). The study will be terminated in the event of severe adverse effects that demonstrate noticeable or statistically significant declines in the primary and secondary outcomes.

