**Methods:**

This study protocol presents a single-blinded multicenter randomized controlled trial that will be carried out in six study centers in Germany and Luxembourg. We included adults with MCI (existing F06.7 ICD-10-GM diagnosis and TICS ≥ 21 and ≤ 32). The intervention group will use a mobile, multi-domain cCT (“NeuroNation MED”) for 12 weeks. Meanwhile, the wait list control group will receive standard medical care or no care. The eligibility of volunteers will be determined through a telephone screening. After completion of the baseline examination, patients will be randomly assigned to one of the experimental conditions in a 2:1 ratio. In total, 286 participants will be included in this study. The primary outcome is the change of cognitive performance measured by the index score of the screening module of the Neuropsychological Assessment Battery. Secondary outcomes are changes in the Cognitive Failures Questionnaire, Hospital Anxiety and Depression Scale, Health-49, Health Literacy Questionnaire, among others. All of the primary and secondary outcomes will be assessed at baseline and after the 12-week post-allocation period. Furthermore, the intervention group will undergo an assessment of the System Usability Scale, and the training data of the NeuroNation MED application will be analyzed.

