### Sample size {14}

The assumed effect size is based on results of previous studies using the cognitive training program “NeuroNation BT” [69] and comparable digital cognitive training applications [25, 26, 36, 70]. A calculation by means of a *t*-test for independent samples was used as the basis for the sample size calculation within the trial described here. With an allocation ratio of 2:1, if 164 subjects are included in the IG and 82 subjects are included in the control group, differences with an effect size of 0.39 or greater can be shown (a priori power analysis, Wilcoxon-Mann–Whitney test (two groups), power = 80%, two tails significance level *α* = 0.05). This resulted in the total sample size of 246. We expect a drop-out rate of approximately 15% [71], which results in a sample size to be recruited of *N* = 286. This sample size calculation was performed with G*Power 3.1.

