### Plans to give access to the full protocol, participant-level data, and statistical code {31c}

Regularly, safety reports are generated and distributed to the Data Safety and Monitoring Committee. The datasets analyzed during the current study will be available from the management committee after the primary publication on reasonable scientific request.

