### Composition of the data monitoring committee, its role and reporting structure {21a}

Data monitoring committee (DMC) is not needed. The trial involves a low-risk intervention and the potential adverse effects are well-understood. Previous studies have shown no significant adverse events or serious safety concerns related to this intervention. Therefore, the likelihood of unexpected safety issues arising during this trial is minimal.

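### The alpha levels 0.00305 and 0.04695 do not follow from a spending function with a look at 50 participants; the error is conservative, but the final threshold and the role of the look need restating

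*Protocol article*

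**What the plan says.** - **Timing of the look** (Interim analyses {21b}): "An interim analysis will be conducted when the sample size reaches 50 participants".
- **Alpha levels** (same section): these are attributed to an alpha-spending function that is not named, and "the alpha level was determined to be 0.00305 for the interim analysis and 0.04695 for the final analysis of the primary outcome". The secondary outcomes are to be tested at 0.00783 after a Bonferroni correction.
- **Action at the look** (same section): the one action given is termination for severe adverse effects showing "noticeable or statistically significant declines in the primary and secondary outcomes". The termination reasons in {11b} are ethics, recruitment, safety, changed clinical practice and early signs of harm. They do not include stopping for efficacy.
- **Sample size** (Sample size {14}): 164 and 82 participants, effect size 0.39, "power = 80%, two tails significance level" 0.05. "This resulted in the total sample size of 246", raised for drop-out. The abstract gives the recruited number: "In total, 286 participants will be included in this study".
- **Oversight**: {21a} says "Data monitoring committee (DMC) is not needed", whereas {31c} says that "safety reports are generated and distributed to the Data Safety and Monitoring Committee".

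**The concern.** A spending function takes the information fraction at the look and returns the alpha that may be used there. The final critical level is then solved from the joint distribution of the two test statistics. The stated pair fails on both steps. The interim figure is the one that the most common function gives for a look at half the sample, not at one fifth. The final figure is a subtraction, not a solved level.

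Alpha is also deducted for a look to which the article attaches no efficacy decision, and the sample size was computed at the undivided 0.05. At stake is the level against which the primary outcome will be judged, together with the secondary level derived from it. A reader who tries to reproduce either from the stated method and timing will fail.

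**Working it through.** **Inputs.** Look at 50 participants ({21b}); 246 analysable, 164 and 82 ({14}); 286 recruited (abstract); two-sided alpha 0.05, effect size 0.39, Wilcoxon-Mann-Whitney test ({14}). The spending function is not given, so the O'Brien-Fleming type is an assumption, tested by whether it returns the stated figure.

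**1. Reproducing the stated pair.** Two-sided O'Brien-Fleming-type (Lan-DeMets) spending is α(t) = 4 × [1 − Φ(z₀.₉₈₇₅ / √t)], with z₀.₉₈₇₅ = 2.2414.
- At t = 0.50: 2.2414 / 0.7071 = 3.170, so α = 0.0030506.
- Remainder: 0.05 − 0.0030506 = 0.0469494.
- Solving α(t) = 0.00305 gives t = 0.49998.

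Both stated figures are returned to five decimals at half the information, which would be 123 of 246 participants.

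**2. The same function at the planned look.**
- t = 50/246 = 0.203: 2.2414 / 0.4508 = 4.972, so α = 0.0000013.
- t = 50/286 = 0.175: 2.2414 / 0.4181 = 5.361, so α = 0.00000017.

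Pocock-type spending at 50/246 gives 0.0150, which does not match either. A less usual function can be tuned to give 0.00305 at t = 0.203: the power family with exponent 1.76, or the Hwang-Shih-DeCani family with γ = −2.45.

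**3. The final nominal level.** The two test statistics have correlation √t. The final level is the value that makes the probability of crossing at either look equal to 0.05.

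| Case | Interim level | Final nominal level |
|---|---|---|
| Look at t = 0.50 | 0.00305 | 0.0490 |
| 0.00305 spent at 50/246, by any function | 0.00305 | 0.0478 |
| O'Brien-Fleming-type spend at 50/246 | 0.0000013 | 0.0500 |

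None of these is 0.04695. The middle row depends only on what was spent and when, so it does not matter which function produced 0.00305.

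**4. Overall type I error of the stated pair.** 0.0491 at t = 0.203, 0.0492 at t = 0.175 and 0.0480 at t = 0.50. If no efficacy claim can be made at the look, only the final test counts and the error is 0.04695. None exceeds 0.05. Pairing 0.00305 at 50/246 with a final level of 0.05 gives 0.0522.

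**5. Power at 246, effect 0.39.** Noncentral t, with group sizes multiplied by 3/π for the Wilcoxon test:
- alpha 0.05: 80.1%, which confirms the planned 246;
- alpha 0.0478: 79.6%;
- alpha 0.04695: 79.4%, and 252 participants would be needed for 80%.

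Power of the look itself at 0.00305, with about 33 and 17 participants, is about 4% (noncentral t).

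**6. Secondary level.** 0.04695 / 6 = 0.007825, which is the stated 0.00783. From 0.0478 it would be 0.00797, and from 0.05 it would be 0.00833.

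**The case against.** The strongest reply is that nothing is inflated. Two levels that sum to 0.05 control the type I error whatever the timing of the look and the correlation between the tests. The cost is under one percentage point of power, and 0.04695 could simply be kept as a Bonferroni-type split. This stands, and it limits the severity. It does not rescue the text, which credits the figures to a spending function.

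The function is unnamed, so the half-sample origin is an inference from a numerical match. This also stands. The second defect does not rest on that inference, because 0.04695 is not the final level for any function that spends 0.00305 at the look.

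The article is a condensed account, so an efficacy rule may exist in the full protocol or analysis plan. That is fair: what can be said is that the article states none.

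Three stronger readings are tempting and are not supported:
- **Site investigators see unblinded interim results.** No section says who runs or sees the interim analysis, and {16b} keeps allocations in a file closed to study staff. Access is an open question, not a stated fact.
- **A final p-value between 0.047 and 0.050 is bound to be misclassified.** If 0.00305 is a live efficacy test at 50 participants, values from 0.0478 to 0.050 are rightly non-significant, and only the strip from 0.04695 to 0.0478 is in dispute. The wider window applies only if no efficacy test is made at the look.
- **The final test should simply return to 0.05.** With a live test at 0.00305 this gives an overall alpha of about 0.052. The trial status section expected the last patient out in November 2023. If that timetable held, the look has passed, and loosening a published threshold afterwards would be hard to defend.

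**Conclusion.** The point holds as an error of derivation. The stated levels do not follow from the stated method and look: 0.00305 fits t = 0.50 and not t = 0.20, and 0.04695 is alpha left to spend rather than a final nominal level. The first part assumes O'Brien-Fleming-type spending. The second requires only that 0.00305 be spent at the look.

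The direction is conservative. Overall error is about 0.0491, or 0.04695 if the look allows no claim, and the loss of power against the planned 80.1% is about 0.7 percentage points. The validity of a positive result is not threatened. What is wrong is a decision threshold that cannot be derived as described, a secondary level that inherits it, and an interim test whose consequence for efficacy is not stated. Severity is minor to moderate.

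The conflict between {21a} and {31c} over a monitoring committee is real but separate, and it changes no alpha level.

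**What to change.** Name the spending function and the information fraction, and state whether the look permits an efficacy claim. The final level then depends on how the look is used:

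1. **If 0.00305 was or will be a live efficacy test at 50 participants:** set the final level to about 0.0478, or keep 0.04695 and describe it as a conservative Bonferroni-type split. Do not use 0.05.
2. **Only if no efficacy test has been made at 50 and the results are still blinded:** make the look harm-only and test the primary outcome at 0.05, or use the levels for the true fraction, 0.0000013 and 0.0500.

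Recompute the secondary level from the final level chosen, and restate the power at that level instead of at 0.05. Separately, reconcile {21a} with {31c}, so that it is clear whether a monitoring committee exists.

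The cost is protocol and analysis-plan wording and a recalculated threshold, with no extra participants. Under the first option the price is at most about 0.7 points of power. Under the second, with the harm-only look, it is an efficacy look that had about a 4% chance of success.

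### Secondary outcomes are tested at 0.00783 each with no link to the S-NAB result; Holm and a gate on confirmatory claims would improve the rule at almost no cost

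*Protocol article*

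**What the plan says.** All of the rule stands in the protocol article, section Interim analyses {21b}. For the primary outcome, "the alpha level was determined to be 0.00305 for the interim analysis and 0.04695 for the final analysis of the primary outcome". For the secondary outcomes: "The alpha level for the secondary outcomes in the final analysis will be adjusted to 0.00783 using the Bonferroni correction". The section gives neither the number of secondary tests nor any condition that ties them to the primary result.

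The abstract lists the secondary scales: "Secondary outcomes are changes in the Cognitive Failures Questionnaire, Hospital Anxiety and Depression Scale, Health-49, Health Literacy Questionnaire, among others". Section Objectives {7} states formal null and alternative hypotheses for the S-NAB only. The secondary effects appear there as a research question: "Does the use of the mobile cCT program lead to an improvement in depressive and anxious symptoms, subjective cognitive functioning", followed by well-being and health-related competence. Section {20b} calls the subgroup analyses, and the analysis of secondary outcomes in the post-COVID group, exploratory. It does not apply that label to the main secondary scales.

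The only overall significance level is in Sample size {14}: "power = 80%, two tails significance level" 0.05, for the comparison on which the trial was sized.

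**The concern.** The secondary level is built from the same 0.04695 that the primary test uses in full. A reader who meets a Bonferroni-corrected threshold will tend to treat a secondary p-value below it as a controlled positive result, and nothing in the article says whether that is allowed when the S-NAB comparison fails.

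The secondary scales are self-reported by participants who know their allocation, in a comparison with a wait list, and section {23} places the trial in the fast-track process for digital health applications. Which results may be claimed, and under what condition, therefore has practical weight.

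There is also a smaller loss. Single-step Bonferroni gives up power that a step-down procedure recovers at the same family-wise level.

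**Working it through.** **Inputs from the article.** Interim alpha 0.00305, final alpha 0.04695 and secondary alpha 0.00783 ({21b}); 164 and 82 participants, effect size 0.39, two-sided 0.05 ({14}); interim at 50 participants ({21b}).

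**Assumed.** Six secondary tests (implied), equally correlated test statistics, and d = 0.39 for the secondary outcomes. The article gives no effect size or correlation for them.

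**1. The plan's own figures.** 0.00305 + 0.04695 = 0.05000. Dividing 0.04695 by 5, 6 and 7 gives 0.00939, 0.007825 and 0.00671, and 0.05/6 = 0.00833. Only 0.04695/6 matches 0.00783.

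**2. Each family alone, all null hypotheses true.**
- Primary, interim plus final: at most 0.05. With the interim at 50 of 246 the exact value is 0.049.
- Six secondaries: at most 6 × 0.00783 = 0.047. Under independence, 1 − (1 − 0.00783)^6 = 0.046.

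**3. Both families together, no gate.** Under independence the final analysis gives 1 − (1 − 0.04695) × (1 − 0.00783)^6 = 0.091. Simulation (1 million draws) gives:

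| Correlation primary–secondary / among secondaries | Final analysis only | With interim |
|---|---|---|
| 0 / 0 | 9.1% | 9.3% |
| 0.2 / 0.3 | 8.7% | 8.9% |
| 0.3 / 0.5 | 8.1% | 8.4% |
| 0.5 / 0.7 | 7.1% | 7.3% |
| 0.7 / 0.8 | 6.1% | 6.4% |

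The upper bound without any assumption on correlation is 0.05 + 0.04698 = 9.7%.

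**4. With a gate.** If all null hypotheses are true, a false claim first requires a false-positive S-NAB result, so the rate is that of the primary: about 4.9%, and never above 5%.

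**5. Bonferroni against Holm.** Holm compares the ordered p-values with 0.04695/6, /5, /4, /3, /2 and /1, that is 0.00783, 0.00939, 0.01174, 0.01565, 0.02348 and 0.04695, and stops at the first failure. The first threshold is the Bonferroni level and the later ones are larger, so Holm rejects everything that Bonferroni rejects.

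The non-centrality is 0.39 × √(164 × 82/246) = 2.88. The two-sided critical value at 0.00783 is 2.66, so Bonferroni power is Φ(2.88 − 2.66) = 0.59. Simulated with correlation 0.5 (400,000 draws), average power per real effect under Holm is 0.62 with three of six effects real and 0.69 with all six.

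**The case against.** A reader might infer that the alpha has been spent twice by mistake, and that the trial runs at 8% to 9% where 5% was planned. The documents do not support that. The 0.05 in {14} belongs to the sample-size calculation, and the two levels in {21b} are expressly for the primary outcome. No section promises 5% across primary and secondary outcomes together. The primary's error rate is untouched by the secondary tests, the secondary family is held below its own level, and treating the two as separate families is an accepted convention.

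Nor does any section say that a secondary result counts as confirmatory after a failed primary. Only the S-NAB has formal hypotheses, and the wording of a research question is not a claim. The status and order of secondary tests are also often settled in a statistical analysis plan, which is not shown here.

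These points stand, and they limit the finding. The 6% to 9% applies only if secondary results are to be claimed independently of the S-NAB. It also rests on an implied count and unknown correlations.

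Two further points are fair. Bonferroni is valid, so Holm is a gain in power and not a repair. And a gate does not remove bias in unblinded self-report; it only limits when such results can be claimed.

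What remains is that the article fixes a numerical rule for the secondary outcomes, and that this rule can be made more powerful and clearer without cost to the primary test.

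**Conclusion.** The multiplicity rule in {21b} is internally valid but can be improved. Primary and secondary families are each controlled, at or below 5% and 4.7%. They are not linked, and the status of a secondary result after a failed primary is left open. If such a result were claimed as confirmatory, the chance of at least one false positive with no true effects would be about 6% to 9%, assuming six tests and correlations from high to zero; a gate brings it to at most 5%. Holm raises average power per real effect from 0.59 to between 0.62 and 0.69 under the assumed d = 0.39 and correlation 0.5. The size of that gain depends on those assumptions; that Holm never rejects fewer hypotheses does not.

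**What to change.** Amend {21b} in two respects, before unblinded final results are seen.

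1. Test the secondary outcomes by Holm's procedure at a family-wise level of 0.04695 in place of Bonferroni, and state the number of tests in the family, since the stepwise thresholds depend on it.
2. State that secondary outcomes are claimed as confirmatory only if the S-NAB group effect is significant at 0.04695 in favour of the intervention group, and are otherwise reported as exploratory.

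This takes one or two sentences, needs no further participants or data, and costs the primary test no power. The price is that, if the primary fails, no secondary result can be claimed as confirmatory, however small its p-value.
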